## 1. Rationale

Interventional trials demonstrated that intensive blood glucose control in patients with type 1 or type 2 diabetes mellitus protects against the onset or progression of long-term micro-vascular complication (1, 2). Insulin therapy is often needed to achieve adequate blood glucose control; it consists injection of a long acting insulin to cover basal needs, and of meal-related short acting insulin. Regarding basal insulin, a preparation with a near peak-less and long-lasting effect that mimics the flat interprandial and basal insulin secretion seen in nondiabetic individuals would be desirable in order to improve glycemic control and to diminish the risk of hypoglycemia (3) .

The human insulin analogues detemir (Levemir®) and glargine (Lantus®) are increasingly used as a basal insulins in type 1 and in type 2 diabetes. Both are long acting insulin analogues indicated for subcutaneous (s.c.) administration. The unique mechanism of protraction of insulin detemir results from a combination of increased self association and albumin binding via the attached C-14 fatty acid, delaying and prolonging absorption (4, 5). Insulin glargine differs from human insulin by replacement of the amino acid asparagine at position A21 by glycine and by the addition of two arginine molecules to the C-terminus of the B-chain (6). After injection into the subcutaneous tissue, the acidic solution of insulin is neutralized, leading to the formation of micro-precipitates from which small amounts of insulin glargine are slowly released (7). The addition of a small amount of zinc (30µg/ml insulin) as a hexamer stabilizing agent further prolongs the duration of action (8).

Previous studies demonstrated both a delayed and a sustained blood glucose-lowering effect with insulin detemir and insulin glargine compared with conventional NPH insulin in healthy subjects (9-11). These results also revealed that a higher molar dose of insulin detemir was needed to achieve comparable glycemic control similar to that observed with NPH insulin (10). Importantly, glucose clamp studies and clinical trials have shown that the variability of the glucose lowering action of insulin detemir and glargine are reduced compared to NPH insulin in diabetic patients. In patients with type 1 diabetes, the mean duration of action of insulin detemir at clinically relevant insulin doses ranged between 12 to 23 hours, while the mean ( $\pm$  SE) duration of action of glargine was  $22 \pm 4$  hours (12, 13). The pharmacokinetics and pharmacodynamics of s.c. injected insulin are dose-dependent. Thus, both the peak and the duration of action were prolonged after injecting increasing doses of regular insulin, rapidly acting insulin analogues or NPH-insulin (14). One study with insulin detemir in patients with type 1 diabetes confirmed a dose-dependent increase in duration of action (12). This is important, as the dosage requirements in type 2 diabetes can be very high, especially in obese subjects with marked insulin resistance. Yki-Järvinen et al reported daily injected doses of up to 168 Units of basal insulin per day (15).

In clinical practice further weight gain with insulin therapy in obese patients with type 2 diabetes is a major barrier to insulin therapy. Interestingly, studies with insulin detemir have shown significantly less weight gain compared to NPH insulin (16). Research concerning the potential mechanisms for this weight-neutral behavior of detemir is ongoing.

In obese patients, doses of up to 1.5-2 U/kg body weight of basal insulin are increasingly used. However, most previous pharmacodynamic studies used lower doses of insulin detemir (0.6 U/kg body weight) (9, 10, 17) or insulin glargine (18-21) and investigated either lean or slightly overweight patients (9, 10, 12, 13, 17-21), but not patients with frank obesity. Thus, pharmacodynamic parameters (maximum action; duration of action) of moderate to high doses of subcutaneously applied detemir and glargine insulin, which are increasingly used in severely obese subjects, have not been reported up to date.

## 2. Objectives:

The primary aim of this study is to compare the dose-response relationship of moderate and of high doses of insulin detemir and of insulin glargine in 12 severely obese type 2 diabetic subjects.

### 1. Primary endpoint:

#### ○ Pharmacodynamics:

- The glucose consumption over time to maintain euglycemia: i.e. the peak of action, the time from peak to half maximal action, the total duration of action will be assessed following a single subcutaneous injection of two different doses of insulin detemir and glargine.
- The total duration of action is defined as the time between the beginning of action (from the time of 50% reduction in intravenous insulin infusion) until the end of action when plasma glucose consistently exceeds 8.3 mmol/l after the glucose infusion had been stopped, or after 36 h, whichever comes first (12, 13) of both doses and of both insulins.
- If the glucose-insulin-lowering effects of the 2 insulins are not equal at identical insulin dosages, the pharmacodynamics will be compared at the same effect level (standardized activity ratio, see below).

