### 3.2.1. Inclusion criteria:

- History of type 2 diabetes mellitus treated with insulin and/or metformin, and/or sulfonylureas
- Age 18-65 years
- Body mass index > 35 kg/m^2
- HbA1c >6.0% and < 10%

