### 3.3.2. Inpatient metabolic studies

Patients eligible to participate in the study based on the results of the screening visit will be admitted to the Department of Medicine, University Hospital Basel ([name]) at 7 am after fasting overnight for approximately 40 h, including an overnight stay. In patients on sulfonylureas these will be discontinued for 4 weeks before beginning the study and be withheld during the total duration of the study. Metformin will be paused 48 h (kinetic wash-out) and long-acting basal insulins will be paused 48-72 h prior to the study. If necessary, short-acting insulin will be given up to the evening prior to the study to keep blood glucose levels below 10 mmol/l.

An intravenous cannula will be inserted into an antecubital vein for the infusion of insulin and glucose. A second intravenous canula will be placed in a dorsal hand vein to obtain frequent blood samples for measurement of plasma glucose concentration.

At the beginning of the study a variable intravenous infusion of human soluble insulin will be started at 8 am to reach euglycemia at a plasma glucose level of 5.5 mmol/l within 30-60 minutes. At 10 am a single subcutaneous injection of either insulin detemir or insulin glargine will be administered in the thigh in two different dosages (0.8 and 1.6 IU/kg body weight) in randomized order. Intravenous regular insulin will be tapered when plasma glucose falls below 5.5 mmol/l.

Plasma glucose will be monitored at frequent intervals every 10 to 30 min (goal: plasma glucose 5.5 mmol/l; total blood needed 2 ml/measurement), and glucose 10% will be

administered by continuous i.v. infusion (syringe pump) using an algorithm to maintain plasma glucose levels at 5.5 mmol/l. Blood will also be drawn every 2 h for the first 6 h and subsequently every 6 h for the measurements of the serum concentrations of C-peptide, insulin detemir and insulin glargine using specific radioimmunoassays.

Each subject will be studied at four occasions in order to study the effects of two different doses (0.8 and 1.6 IU/kg body weight) of insulin detemir and of insulin glargine,, respectively. The procedures will be identical during each study. The time period between the different studieis always at least 7 days.

Each inpatient metabolic study will last 36 hours after the injection of insulin detemir or until the plasma glucose will consistently increase to > 8.3 mmol/l in the absence of glucose infusion.

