#### 3.5.2. Null-hypothesis for the secondary endpoint:

With increasing dosage, the mean duration of action of insulin detemir and insulin glargine will not last over 30 hours

The plasma peak insulin levels and the time from the respective peak levels to half max levels at the two dosages of both insulins will not be different.

The total glucose consumption and the duration of action of the insulins is not correlated to the degree of obesity, i.e. of body mass index and of body composition (central fat accumulation) in obese patients with type 2 diabetes mellitus.

Both insulins (glargine and detemir) are dose-equivalent in terms of their glucose-lowering effect in obese patients with type 2 diabetes mellitus.

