#### 3.5.3. Measurements and calculations

Performance of an euglycemic hyperinsulinemic clamp by hourly measurement of plasma glucose, insulin and C-peptide and calculation of the area under the curve (AUC) of the necessary glucose infusion rate (GIR) which is necessary to maintain plasma glucose at 5 mmol/l. For serum insulin and serum C-peptide, descriptive statistics for pharmacokinetic measures are performed (maximal serum insulin concentration [Cmax], time to Cmax [tmax], and AUC; minimal serum C-peptide concentration [Cmin], time to Cmin [tmin] and AUC).

End of insulin action is defined as the time at which plasma glucose consistently increases to > 8.3 mmol/l despite adaptation of glucose infusion.

Since it is debated, that a given unit of insulin detemir is equipotent to a given unit of insulin glargine, we compare the activity ratio (standardized activity ratio) of the two insulins by the total glucose consumption (g glucose/U of insulin administered). This activity ratio will be used to determine further pharmacodynamic effects like the peak of action, the time from peak to half maximal action and the total duration of action.

We will perform a mixed model with a random subject effect in order to calculate differences between the two different dosages and the different insulins (total glucose consumption, duration of action). Among others, covariates that will be assessed include BMI, age, sex.

As there are several primary endpoints, a Bonferroni correction will be applied.

The sample size is small, but was determined by specifying a 95% CI with a relative width of 30% for the duration of action (12). However, as previous studies have used lower total insulin dosages and studied patients for maximal 24 hours, a very meaningful sample size calculation cannot be performed.

1ml of additional serum and plasma will be stored for batch analysis of cytokines and not yet defined parameters (not part of this protocol)

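### Total duration of action is cut off at 36 h with neither a censoring rule nor a restricted-duration label, and its clock and its end are each described in two ways

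*Protocol*

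**What the plan says.** Protocol section 2 (Primary endpoint, Pharmacodynamics) lists several quantities, among them total duration of action. Duration is "the time between the beginning of action (from the time of 50% reduction in intravenous insulin infusion") up to the end of action, which is reached when "plasma glucose consistently exceeds 8.3 mmol/l after the glucose infusion had been stopped, or after 36 h, whichever comes first".

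Section 3.3.2 sets the length of observation: "Each inpatient metabolic study will last 36 hours after the injection of insulin detemir", or until glucose rises above 8.3 mmol/l with no glucose being infused.

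Section 3.5.3 defines the end again: "End of insulin action is defined as the time at which plasma glucose consistently increases to > 8.3 mmol/l" even though the glucose infusion is adapted. No 36 h limit appears there. The analysis of total glucose consumption and duration is one sentence: "We will perform a mixed model with a random subject effect in order to calculate differences between the two different dosages and the different insulins".

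Two hypotheses use the result. Section 3.5.1 compares mean duration between the insulins and the doses. Section 3.5.2 states a secondary null: "With increasing dosage, the mean duration of action of insulin detemir and insulin glargine will not last over 30 hours".

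**The concern.** A clamp in which insulin is still acting at 36 h shows only that the duration is at least that long. The section 2 definition nevertheless gives it the cut-off as its end of action, and the named model has no term for a lower bound. The endpoint is called total duration, so a reader will take the resulting mean as the time the insulin acts.

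The cut-off lies where the trial looks for its answer. Sections 1 and 6 expect longer action at higher doses, and the trial goes to 1.6 IU/kg. The secondary hypothesis sits at 30 h, only 6 h below the cap. Section 3.5.3 concedes that earlier studies used lower doses and at most 24 h of observation. At stake are the high-versus-moderate dose contrast, the insulin contrast at the high dose, and the 30 h question.

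**Working it through.** **1. The passages side by side.**

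- *Clock.* Duration starts at onset (section 2); observation stops 36 h after injection (section 3.3.2). The longest observable duration is 36 h minus onset, and it varies by clamp. Section 2 does not say where its own 36 h starts. If it started at onset, it could never be reached, because observation would already have ended.
- *End of action.* A clamp that never exceeds 8.3 mmol/l ends at 36 h under section 2. Under section 3.5.3 it has no end of action at all.
- *Model.* Neither section says how such a clamp enters the mixed model.

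**2. The plan's own figure.** Section 3.5.3 bases the 12 subjects on a 95% CI of relative width 30% for duration, but gives no SD. If 30% is the full width, 2.201 × CV / √12 = 0.15, so CV = 0.236. That is an SD of 6.1 h at a mean of 26 h and 7.1 h at 30 h. If 30% is the half width, CV = 0.47. So n = 12 cannot be verified, and the SD must be assumed. Section 1 gives 22 ± 4 h for glargine, labelled SE. I use SD 4 to 7 h.

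**3. Formula.** For normal durations with mean μ and SD σ, cut at c, put a = (c − μ)/σ. Then:

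- mean of the capped duration = μ − σ[φ(a) − a(1 − Φ(a))]
- proportion capped = 1 − Φ(a)

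Example: μ = 34, σ = 4, c = 36 gives a = 0.5. The bracket is 0.3521 − 0.5 × 0.3085 = 0.1978, so the bias is −4 × 0.1978 = −0.79 h, with 31% capped.

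**4. Range.** Each cell runs from SD 4 h to SD 7 h. The 34 h ceiling assumes onset 2 h after injection; the protocol gives no onset figure.

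| True mean | Capped, 36 h | Mean too low by, 36 h | Capped, 34 h | Mean too low by, 34 h |
|---|---|---|---|---|
| 26 h | 1–8% | 0.01–0.24 h | 2–13% | 0.03–0.44 h |
| 30 h | 7–20% | 0.12–0.76 h | 16–28% | 0.33–1.24 h |
| 34 h | 31–39% | 0.79–1.91 h | 50% | 1.60–2.79 h |

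**5. Contrasts.** Assume a between-subject SD of 4 h and a within-subject SD of 5 h, so the total SD is √(16 + 25) = 6.4 h.

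- Dose effect, true 28 versus 36 h, cap 36 h: the capped means are 27.68 and 33.45 h, so 8 h appears as 5.8 h. With a 34 h ceiling it appears as 4.9 h.
- Insulin difference at the high dose, true 32 versus 36 h, cap 36 h: the capped means are 30.96 and 33.45 h, so 4 h appears as 2.5 h.
- Lower durations, true 22 versus 26 h, cap 36 h: 4 h appears as 3.9 h, so little is lost.

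**6. The 30 h question.** A cap can only lower the mean, so it makes a mean above 30 h harder to show. The protocol names no test. With an assumed one-sided 5% test, 12 subjects, SD 6.4 h and a true mean of 33 h, simulated power falls from 45% to 36%. Whether a given clamp lasts beyond 30 h can still be read off whenever onset is less than 36 − 30 = 6 h after injection.

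**The case against.** The strongest reply is that nothing is wrong with the model. A duration ended by whichever event comes first can be read as a restricted duration, and a mixed model estimates its mean validly. An unseen SAP may also say how unfinished clamps are handled. The first part stands as a possible repair, but the protocol calls the quantity total duration and declares no restriction. The second does not dispose of the point: the cap, the two clocks, the two definitions and the model are all fixed in the protocol text.

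It is also fair that the only durations documented are 12 to 23 h for detemir and 22 h for glargine, in type 1 diabetes and mostly at lower doses. Near those values the cap does almost nothing. The losses in step 5 depend on assumed high-dose means of 32 to 36 h.

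Four stronger readings are tempting and are not supported:

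- *The cap creates a false insulin-by-dose interaction.* The protocol plans no interaction test.
- *The cap invalidates the primary test.* If two conditions have equal duration distributions and similar onset, they are capped alike, so the test stays essentially valid and the harm is attenuation. In the step 5 setting (means 24 and 32 h for one insulin, 28 and 36 h for the other; 12 subjects, paired contrasts, two-sided 5%), simulated power for the dose main effect moves only from 99.8% to 99.6%. For the insulin main effect it falls from 71% to 64%, and for the insulins at the high dose from 43% to 34%.
- *Time from peak to half-maximal action is cut off in the same way.* Section 2 attaches the 36 h limit only to total duration, and half-maximal action comes before its end.
- *Patients' own insulin carries them to the ceiling.* Entry at "HbA1c >6.0% and < 10" per cent, with metformin allowed as the only treatment, makes this conceivable. The documents give no rate, each patient is their own control, and a censored model would not repair it.

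**Conclusion.** The point holds as a should-fix on one of several primary endpoints. Following the text as written, clamps still active at the cut-off contribute too short a total duration. With similar spread and onset across conditions, the longer-acting condition loses more, so dose and insulin contrasts shrink and the 30 h question becomes conservative.

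The direction follows from the definition; the size does not. Under normal durations and SD 4 to 7 h, the cap is negligible if high-dose means stay in the mid-20s and grows material as they pass about 30 h, the region section 3.5.2 asks about. A ceiling below 36 h, because of onset, makes it larger. If onset differs between the insulins, their ceilings differ too, and the protocol gives nothing to size that. A reader might infer that the duration results would be worthless; the calculations show attenuation that depends on where the true means lie.

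**What to change.** First reconcile sections 2, 3.3.2 and 3.5.3, so that there is one definition of the end of action and one stated origin for the 36 h. Which definition is right is for the investigators to decide. Then choose one of two routes:

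- Flag clamps not ended by 36 h after injection as right-censored at 36 h minus onset, and analyse duration with a censored (Tobit-type) mixed model or a survival model with a subject frailty.
- Declare the endpoint as duration restricted to 36 h after injection, drop the word total, and keep the mixed model.

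Under either route, report the number of capped clamps per insulin and dose. Answer the 30 h question from the censored model or as the proportion of clamps lasting beyond 30 h.

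No extra data or procedures are needed. The first route costs somewhat more complex modelling and relies on a distributional assumption that 12 subjects can hardly check. The second costs a more modest claim for the endpoint.

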### 2. Secondary endpoints:

#### ○ Pharmacokinetics:

- The plasma peak detemir and glargine levels and the time from the respective peak levels to half maximum levels at the two dosages of both insulins
- The mean duration of insulin as defined by appropriately elevated detemir and glargine levels at each of the two dosages.
- The dose-equivalence of both, insulin glargine and detemir in terms of their glucose-lowering effect in obese patients with type 2 diabetes mellitus.

#### ○ Other:

- The total glucose consumption and the duration of action of the two insulins as a function of the degree of obesity, i.e. of body mass index and central obesity (waist circumference) in obese patients with type 2 diabetes mellitus.

## 3. Trial design and methods

### 3.1. Trial drugs

Insulin detemir (Levemir®) will be provided by NovoNordisk Pharma AG, Küsnacht, Switzerland. Insulin glargine (Lantus®, Sanofi-Aventis, Meyrin, Switzerland) will be obtained from the hospital pharmacy, University hospital Basel, Switzerland.

### 3.2. Trial population:

Twelve morbidly obese subjects with type 2 diabetes (BMI >35 kg/m^2) will be recruited from the outpatient clinic of the Division of Endocrinology, Diabetes and Clinical Nutrition at the University Hospital Basel.

### 3.2.1. Inclusion criteria:

- History of type 2 diabetes mellitus treated with insulin and/or metformin, and/or sulfonylureas
- Age 18-65 years
- Body mass index > 35 kg/m^2
- HbA1c >6.0% and < 10%

### 3.2.2. Exclusion criteria:

- Patients treated with thiazolidinediones (glitazones)
- Any significant or active hepatic, cardiovascular, pulmonary, renal, neurological, musculoskeletal, hematological or endocrine disease.
- Pregnant or breast feeding women
- Woman of childbearing potential not using a reliable method of birth control such as oral contraceptives or an IUD.
- Subjects refusing or being unable to give written informed consent

## 3.3. **Trial schedule:**

### 3.3.1. Screening visit:

Patients admitted to the outpatient clinic of the Division of Endocrinology, Diabetes and Clinical Nutrition of the University Hospital Basel who are deemed eligible to participate based on medical history and clinical findings will be given a detailed explanation of the study protocol. After obtaining written informed consent a brief physical examination (including, blood pressure, heart rate, body weight and height, waist circumference) will be performed, and a baseline blood sample (including WBC, RBC, creatinine, electrolytes, liver enzymes, lipid profile) will be obtained. A pregnancy test will be obtained in women with childbearing potential.

### 3.3.2. Inpatient metabolic studies

Patients eligible to participate in the study based on the results of the screening visit will be admitted to the Department of Medicine, University Hospital Basel ([name]) at 7 am after fasting overnight for approximately 40 h, including an overnight stay. In patients on sulfonylureas these will be discontinued for 4 weeks before beginning the study and be withheld during the total duration of the study. Metformin will be paused 48 h (kinetic wash-out) and long-acting basal insulins will be paused 48-72 h prior to the study. If necessary, short-acting insulin will be given up to the evening prior to the study to keep blood glucose levels below 10 mmol/l.

An intravenous cannula will be inserted into an antecubital vein for the infusion of insulin and glucose. A second intravenous canula will be placed in a dorsal hand vein to obtain frequent blood samples for measurement of plasma glucose concentration.

At the beginning of the study a variable intravenous infusion of human soluble insulin will be started at 8 am to reach euglycemia at a plasma glucose level of 5.5 mmol/l within 30-60 minutes. At 10 am a single subcutaneous injection of either insulin detemir or insulin glargine will be administered in the thigh in two different dosages (0.8 and 1.6 IU/kg body weight) in randomized order. Intravenous regular insulin will be tapered when plasma glucose falls below 5.5 mmol/l.

Plasma glucose will be monitored at frequent intervals every 10 to 30 min (goal: plasma glucose 5.5 mmol/l; total blood needed 2 ml/measurement), and glucose 10% will be

administered by continuous i.v. infusion (syringe pump) using an algorithm to maintain plasma glucose levels at 5.5 mmol/l. Blood will also be drawn every 2 h for the first 6 h and subsequently every 6 h for the measurements of the serum concentrations of C-peptide, insulin detemir and insulin glargine using specific radioimmunoassays.

Each subject will be studied at four occasions in order to study the effects of two different doses (0.8 and 1.6 IU/kg body weight) of insulin detemir and of insulin glargine,, respectively. The procedures will be identical during each study. The time period between the different studieis always at least 7 days.

Each inpatient metabolic study will last 36 hours after the injection of insulin detemir or until the plasma glucose will consistently increase to > 8.3 mmol/l in the absence of glucose infusion.

Subjects will not be permitted to eat during the inpatient study, but will be given a dinner meal after the end of the study before leaving the hospital. Noncaloric drinks will be given ad libitum throughout the study procedure. Patients will be blinded regarding the dose and type of insulin.

For each patient, the entire study will be finished after the fourth inpatient study has been completed.

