### **3.4. Potential risks and adverse events**

#### **3.4.1. Potential risks:**

We consider the risks of this study to be small.

The specific risks are:

Blood Loss: The total blood loss for both parts of the study will be approximately 800 ml. Patients with pre-existing anemia will be excluded and we will consult patients not to donate blood 4-5 months before and after the study. The 4 parts of the study will be spread over 4 months.

Intravenous catheters: Intravenous catheters used during the clamp are associated with a mild to moderate degree of pain upon insertion, and a small risk of localized infection.

Euglycemic clamp: The euglycemic clamp is a safe technique, which has been used by our group for more than 10 years without any side effects. The insulin doses increase plasma insulin levels to concentrations in the range of fasting to low post-prandial concentrations, and will be gradually decreased as soon as the subcutaneously injected insulin detemir will start its effect. The risk of hypoglycemia during the clamp is minimal since 10% glucose is being infused and plasma glucose is monitored every 10-30 min.

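### One patient's four sessions may start from different states; the named covariates are fixed per patient and cannot reduce that noise, while an available pre-injection baseline is not named

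*Protocol*

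**What the plan says.** The design is a crossover: 12 patients, four clamp sessions each, two insulins at two doses, in randomised order.

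Section 3.3.2 sets the preparation for a session:

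- **Basal insulin:** "long-acting basal insulins will be paused 48-72 h prior to the study". This is a 24 h range, not tied to patient or session. Metformin, by contrast, gets a single value of 48 h.
- **Bridging:** "If necessary, short-acting insulin will be given up to the evening prior to the study to keep blood glucose levels below 10 mmol/l".
- **Sulfonylureas:** "discontinued for 4 weeks before beginning the study and be withheld during the total duration of the study".
- **Spacing:** "The time period between the different studieis always at least 7 days". Section 3.4.1 adds: "The 4 parts of the study will be spread over 4 months".

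The same section also states in general terms that every session follows the same procedures. I.v. insulin starts at 8 am and the study insulin is injected at 10 am. Section 2 (primary endpoint) dates the onset of action from a halving of the i.v. insulin infusion.

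Section 3.5.3 plans a mixed model with a random subject effect for total glucose consumption and duration of action, and says: "Among others, covariates that will be assessed include BMI, age, sex". It names neither a session-level baseline nor a period term.

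**The concern.** A crossover is efficient because each patient is his or her own control. That works best when the patient arrives in a similar state each time. Here two features of the preparation can differ between one patient's sessions. The basal insulin pause may take any value from 48 to 72 h. Time off sulfonylurea must lengthen from the first session to the last in patients who took it. Insulin already on board and insulin sensitivity on the day could both influence glucose consumption and duration of action, so such differences would enter the within-patient residual.

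The covariates that the protocol names do not vary between a patient's sessions: sex is fixed, age is practically so, and weight and height are stated as measured at screening only (section 3.3.1). They can explain differences between patients, but not differences between one patient's sessions. Meanwhile the run-in yields a direct reading of that day's insulin requirement, and the plan does not name it. With 12 patients, the precision of the contrasts between insulins and doses is at stake.

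**Working it through.** The protocol gives no figure for session-to-session variability. Its sample-size statement (12 patients, 95% CI with relative width 30%) gives no SD and cannot be reproduced, and this point does not depend on it.

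**1. Time off sulfonylurea.** Inputs: 4 weeks before the start, withheld throughout, gaps of at least 7 days, sessions spread over 4 months (sections 3.3.2 and 3.4.1). One month = 365.25/12/7 = 4.348 weeks.

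- First session: 4 weeks.
- Last session, minimum gaps: 4 + 3 × 1 = 7 weeks.
- Last session, monthly sessions: 4 + 3 × 4.348 = 17.0 weeks.
- Last session, a full 4 months from first to last: 4 + 4 × 4.348 = 21.4 weeks.

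The increase is certain in sulfonylurea users. Its size depends on spacing, and 21 weeks is the upper reading.

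**2. What patient-level covariates can do.** With all four sessions present, a term that is constant within a patient cancels from that patient's treatment differences. A simulated 12 × 4 crossover (random order per patient, within-patient SD 1, subject effects fitted, 1,500 runs per scenario) agrees: adding three patient-level covariates changed a pairwise treatment contrast by at most 3e-14, which is rounding error.

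**3. What a session-level baseline can do.** Let r be the within-patient correlation between the pre-injection i.v. insulin rate and the outcome. Residual variance is multiplied by 1 − r², so the standard error falls by 1 − √(1 − r²). The protocol gives no r; the values are assumptions.

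| r | 1 − r² | SE reduction (formula) | Simulated SE, without → with baseline |
|---|---|---|---|
| 0.3 | 0.91 | 4.6% | 0.41 → 0.40 |
| 0.5 | 0.75 | 13.4% | 0.40 → 0.35 |
| 0.7 | 0.51 | 28.6% | 0.41 → 0.30 |

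The unadjusted value agrees with √(2/12) = 0.408. The simulated gains are slightly below the formula (for r = 0.3: (0.406 − 0.395)/0.406 = 2.7%), partly because the slope must be estimated.

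**4. Cost.** There are 12 × 4 = 48 sessions. After 12 subject effects and 3 treatment contrasts, 48 − 12 − 3 = 33 residual degrees of freedom remain; the covariate leaves 32.

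**5. Bias or noise.** An assumed drift of 2 within-patient SDs from session 1 to session 4 in half the patients raised the unadjusted SE to 0.47–0.49. With the baseline it was 0.39, 0.37 and 0.30 for r = 0.3, 0.5 and 0.7. That is optimistic, because the simulated baseline captures the drift completely. The mean error of the contrast was at most 0.02 in every model and scenario: randomised order turns drift into noise.

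**The case against.** The strongest reply has several parts.

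- **Identical procedures.** Section 3.3.2 says that the sessions follow the same procedures, so 48–72 h may be a range across patients. That reading is possible. The text does not settle it, since the same range rule applied each time still permits different lengths. It remains a point to clarify, not a demonstrated inconsistency.
- **Open covariate list.** The list is introduced as non-exhaustive, and a statistical analysis plan, not shown, may add a session baseline. This stands: the plan does not exclude the adjustment, and the limitation concerns only the three named covariates. An analysis plan cannot, however, recover a pause length that was never recorded.
- **Randomised order.** A reader might infer that unequal starting states would bias one insulin against the other. The documents do not support this. Chance imbalance is ordinary sampling error and is reflected in the standard error.
- **Residual home insulin.** A reader might infer that home insulin is still acting at 48 h. The protocol does not show it. It quotes 12 to 23 h for detemir and 22 ± 4 h for glargine, tests a 30 h threshold and observes for 36 h, all below 48 h. The quoted durations come from type 1 diabetes, and section 1 says high doses in severe obesity are unstudied, so the effect is unknown either way. Glycaemic drift after the 4-week sulfonylurea wash-out is likewise possible but not shown.
- **Spacing.** A reader might see a conflict between "always at least 7 days" and a spread over 4 months. There is none: one is a minimum gap, the other a total span, and both can hold.
- **The baseline is part of the endpoint.** The pre-injection rate sets the threshold for onset. This does not disqualify it: it is measured before the injection, so that session's treatment cannot affect it.

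**Conclusion.** The point holds as one of precision and clarity. Section 3.3.2 leaves open whether the basal insulin pause is constant across a patient's sessions, and time off sulfonylurea necessarily grows over the study in those who took it. Any resulting variation widens the intervals for the within-patient contrasts; it does not systematically favour an insulin or a dose. BMI, age and sex cannot reduce it.

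The size of the benefit rests on an assumed correlation. At 0.5 or above, a saving of 13% or more in standard error is worth having with 12 patients; at 0.3 it is slight. The preparation issue concerns only patients on basal insulin or sulfonylureas, whose shares are not given. The adjustment itself does not depend on those shares, because it can absorb any session-to-session difference in insulin requirement, whatever its source.

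**What to change.** - **Section 3.5.3:** pre-specify the session's own pre-injection i.v. insulin rate, for example the mean over the last 30 min before 10 am, as a session-level covariate in the mixed model for total glucose consumption and duration of action. Entering it as the deviation from the patient's own mean over sessions, alongside that mean, keeps the slope a within-patient one, as in the calculation above.
- **Section 3.3.2:** reconcile the 48–72 h range with the statement that sessions are identical, by saying whether the pause is constant within a patient. Record the actual pause at each session. The length of the pause and the use of short-acting insulin remain for the investigators.

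The cost is one within-patient degree of freedom out of 33, one recorded time per session and a sentence in each section. The infusion rate must already be available for the onset definition. If the investigators choose a constant pause, scheduling becomes slightly less flexible.
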